### Statistical analysis plan

Sample size was determined a priori using data from an independent pilot study that applied the same eccentric exercise protocol as the present trial. The pilot included 20 participants (five per group) allocated to placebo, 6 J, 24 J, or 72 J PBM, with MVIC assessed before and immediately, 24, and 48 h after exercise. The pilot MVIC data yielded a within-participant correlation of 0.79, a Greenhouse–Geisser correction of ε = 0.82, and an observed group × time effect of f ≈ 0.23. The pilot-derived effect size was estimated from the group × time interaction using a repeated-measures ANOVA framework. Given the small pilot sample and the absence of an IPC group and 72-hour assessment, a conservative planning effect size of f = 0.12 was adopted. Using G*Power 3.1 (Heinrich-Heine-Universität Düsseldorf, Germany), the sample size was calculated for a three-group repeated-measures design with five measurements, α = 0.05, 80% power, f = 0.12, a within-participant correlation of 0.79, and ε = 0.82. The resulting minimum sample was approximately 44 participants; therefore, 45 participants (15 per group) were planned to ensure balanced allocation. Although the calculation used a repeated-measures ANOVA framework, linear mixed-effects models were prespecified for the primary analysis because they better accommodate within-participant correlations and incomplete repeated measurements.

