Normality and homoscedasticity of residuals will be evaluated through graphical inspection (Q-Q plots and residual-versus-fitted plots) and the Shapiro–Wilk test. Potential influential observations and model fit will also be examined using standard diagnostic procedures. Descriptive statistics will be presented as mean ± standard deviation and 95% confidence intervals. The primary endpoint will be MVIC. The primary hypothesis concerns differences in the post-exercise MVIC recovery trajectory among the PBM, IPC, and sham groups. The primary inferential test will be the group × time interaction from a linear mixed-effects model including group and time (treated as categorical factors) as fixed effects, with a participant-specific random intercept to account for within-participant correlations. The prespecified key contrast will be the between-group difference in change in MVIC from baseline to 72 h between the PBM and IPC groups. Additional pairwise contrasts (PBM vs. sham and IPC vs. sham) and analyses of secondary outcomes will be considered exploratory and will not be subject to multiplicity adjustment. The effect measure for the PBM versus IPC comparison will be the between-group difference in change in MVIC from baseline to 72 h, reported with its 95% confidence interval and standardized effect size. Secondary continuous outcomes will be analyzed using linear mixed-effects models and interpreted as exploratory. For ordinal or bounded outcomes, generalized linear mixed-effects models with an appropriate distribution and link function will be used when the assumptions of a Gaussian model are not satisfied.

All randomized participants will constitute the intention-to-treat population and will be analyzed according to their originally assigned groups, regardless of intervention adherence or outcome availability. Missing observations will be handled within the prespecified mixed-effects framework using maximum likelihood estimation under a missing-at-random assumption. Sensitivity analyses comparing the primary maximum-likelihood analysis with a complete-case analysis will be performed if missing outcome data exceed 10% of the primary outcome observations. Statistical significance will be set at *p* < 0.05 for all analyses.

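### The plan names maximum likelihood for the primary mixed model; read literally, with 45 participants, the usual uncorrected interaction tests run at about 6.5% to 7.8% rather than 5%

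*Protocol article*

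**What the plan says.** All the relevant text is in the Statistical analysis plan section of the protocol article.

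- Primary test: "The primary inferential test will be the group × time interaction from a linear mixed-effects model". Group and time are categorical, and the model is fitted "with a participant-specific random intercept to account for within-participant correlations".
- Estimator, first mention, in the missing-data paragraph: "Missing observations will be handled within the prespecified mixed-effects framework using maximum likelihood estimation under a missing-at-random assumption".
- Estimator, second mention, where the primary model is set against an alternative: "Sensitivity analyses comparing the primary maximum-likelihood analysis with a complete-case analysis".
- Threshold: "Statistical significance will be set at *p* < 0.05 for all analyses".
- Design: "the sample size was calculated for a three-group repeated-measures design with five measurements", with 45 participants planned, 15 per group.
- Key contrast: the PBM versus IPC difference in MVIC change from baseline to 72 h, reported with a 95% confidence interval.

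The section does not mention REML, a small-sample correction, the form of the interaction test (likelihood-ratio, Wald chi-square or F) or a denominator degrees-of-freedom method.

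**The concern.** ML estimates the variance components as if the fixed effects were known. The primary model estimates 15 cell means (3 groups × 5 times) from 45 people, so the resulting downward bias is not negligible. Variances that are too small make the interaction statistic too large and the intervals too narrow, always in the direction of finding an effect.

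Two results are affected: the only confirmatory test, and the interval for the PBM versus IPC difference, which is the stated effect measure. ML brings no missing-data advantage in exchange. REML uses the same incomplete records under the same missing-at-random assumption.

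**Working it through.** **Inputs, all from the Statistical analysis plan section.** k = 3 groups, m = 5 measurements, N = 45, α = 0.05, random intercept only (compound symmetry). The correlation of 0.79 used for planning enters only the simulation; the exact results below do not depend on it.

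**Degrees of freedom and divisors (complete, balanced data).**
- Interaction df = (3 − 1)(5 − 1) = 8.
- Within-participant residual df = (45 − 3)(5 − 1) = 168. REML divides the residual sum of squares by this.
- ML divides the same sum of squares by 45 × (5 − 1) = 180.
- Variance ratio ML/REML = 168/180 = 0.933, so variances are 6.7% too low. The between-participant stratum has the same ratio, 42/45 = 0.933.
- Standard-error ratio = √0.933 = 0.966, so standard errors are 3.4% too small.

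**The stated 5% level.** Under REML the interaction test is the ordinary F(8, 168). Its 5% critical value is 1.994, and it delivers exactly 5.0%. The plan's level is therefore reproduced under REML with an F reference.

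**The same test under ML.** Let F be the correctly scaled statistic, distributed F(8, 168) under the null. ML multiplies it by 180/168 = 1.0714. Each ML test therefore rejects when F exceeds a lower cut-off:

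| Test | Rejects when F exceeds | Type I error |
|---|---|---|
| REML, F(8, 168) | 1.994 | 5.0% |
| REML, Wald chi-square | 15.507/8 = 1.938 | 5.7% |
| ML, likelihood-ratio: 180·ln(1 + 8F/168) > 15.507 | 21 × (e^(15.507/180) − 1) = 1.889 | 6.5% |
| ML, F on 168 df | 1.994 × 0.933 = 1.861 | 6.9% |
| ML, F on 180 df | 1.990 × 0.933 = 1.857 | 7.0% |
| ML, Wald chi-square | 1.938 × 0.933 = 1.809 | 7.8% |

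**How much is due to ML.** With an F reference ML adds 6.9 − 5.0 = 1.9 points. With a chi-square reference it adds 7.8 − 5.7 = 2.1 points. The remaining 5.7 − 5.0 = 0.7 points of the Wald chi-square excess come from the reference distribution and would be there under REML too.

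**Key contrast (PBM versus IPC, baseline to 72 h).** The true reference is t on 168 df.
- ML with a t reference: cut-off 1.974 × 0.966 = 1.907, two-sided error 5.8%.
- ML with a normal reference: cut-off 1.960 × 0.966 = 1.894, two-sided error 6.0%.
- REML for comparison: 5.0% (t) and 5.2% (normal).
- Coverage of the nominal 95% interval under ML is thus 94.2% to 94.0%.

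**Simulation check (correlation 0.79, compound symmetry).** With complete data (6,000 runs), ML gave 6.2% (likelihood-ratio), 6.8% (F) and 7.6% (chi-square), and REML with F gave 4.9%. With 10% of the post-baseline values missing, an assumed rate (4,000 runs), ML gave 6.8%, 7.2% and 8.3%, and REML with F gave 5.05%.

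**Limit of the remedy.** Under an assumed covariance that is not compound-symmetric (mean correlation about 0.79, ε about 0.82, matching the planning figures), the REML F test from the random-intercept model ran at about 6.7%, and the ML tests at about 8.1% to 9.4% (4,000 runs). The 6.7% reflects the covariance structure; ML adds to it.

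**The case against.** The strongest counter-argument is that the article does not fix an error rate. The first mention of the estimator is in a sentence about missing data, where the term can loosely cover restricted maximum likelihood. The second serves to contrast with a complete-case analysis. The sentence defining the primary model names no estimator. The test statistic and degrees-of-freedom method are details that a condensed article may leave to a fuller analysis plan, and their absence is no fault here.

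Much of this stands. A reader might infer that the trial will certainly run at 7% to 8%. The document does not support that, because the figure depends on an unstated test. An F test with ML variances but a conservative 42 or 45 denominator df would come out at 4.6% or 4.8%, although only because two errors offset each other. The effect on the key contrast is also small, and with complete balanced data the point estimates do not change.

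What does not stand is that nothing has been specified. The second mention describes the primary analysis as a maximum-likelihood one, so an estimator is stated, and a fuller plan that follows the wording would carry the bias forward. If REML was meant, the text leaves open two estimators that give different p-values from the same data, and the same edit settles it.

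A reader might also infer that changing to REML guarantees 5%. It does so only if the random-intercept covariance is right. The pilot ε of 0.82 gives some reason for doubt, and that is a separate matter from the choice of estimator.

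**Conclusion.** The concern holds as a conditional one. Taken literally, the named estimator biases variances down by 6.7% and standard errors by 3.4%. The primary test then runs at about 6.5% (likelihood-ratio), 6.9% to 7.0% (F) or 7.8% (Wald chi-square), and the key contrast at 5.8% to 6.0%.

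These figures assume complete data, 15 per group, a true random-intercept model, and a test with no small-sample correction or with residual-type degrees of freedom. Missing data at an assumed 10% raise the interaction figures slightly. The inflation is modest, but it affects the only confirmatory test, in the optimistic direction, and is easily avoided. The documents do not establish that any one of these rates will apply.

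**What to change.** In both sentences of the Statistical analysis plan section that name the estimator, replace maximum likelihood with restricted maximum likelihood. State that the interaction test and the PBM versus IPC contrast use Kenward-Roger or Satterthwaite degrees of freedom. Keep the missing-at-random assumption as it is.

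The cost is two phrases and a standard software option, and recruitment had not begun at submission. Significance becomes slightly harder to reach: for complete data the F cut-off on the correctly scaled statistic rises from 1.861 to 1.994. If the sponsor prefers to keep ML, the plan should justify it and name the small-sample correction. The adequacy of the random-intercept covariance needs its own answer, since this change does not address it.

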## Abstract

Exercise-induced muscle damage (EIMD) occurs after unaccustomed eccentric exercise and may impair muscle recovery. Preconditioning with photobiomodulation (PBM) or ischemic preconditioning (IPC) may mitigate EIMD; however, no study has directly compared their effectiveness. This study aims to compare the effects of PBM and IPC applied prior to eccentric exercise on indirect markers of EIMD and associated perceptual responses. We hypothesized that MVIC trajectories would differ among the PBM, IPC, and sham groups, with PBM expected to provide greater preservation of MVIC than IPC. A prospective, randomized, placebo-controlled clinical trial with concealed allocation, blinded outcome assessors and statistician, and intention-to-treat analysis will be conducted. Healthy men (18–35 years) will be randomly allocated to PBM, IPC, or sham groups (n = 15 per group). After the intervention, participants will perform an eccentric exercise protocol for the elbow flexors consisting of 30 repetitions using a dumbbell load numerically matched to maximal voluntary isometric contraction (MVIC) values, with 45-second rest intervals. The primary outcome will be MVIC. Secondary outcomes include rate of force development, delayed-onset muscle soreness, pressure pain threshold, ultrasound echo intensity, range of motion, perceived exertion, and affective responses. Outcomes will be assessed at baseline, immediately after exercise (only MVIC), and at 24-, 48-, and 72-hours post-exercise. The primary analysis will assess the group × time interaction on MVIC using linear mixed-effects models, while secondary outcomes will be analyzed exploratorily. This study will provide, to our knowledge, the first direct comparison between PBM and IPC as preconditioning strategies to attenuate EIMD. The findings may help determine the most effective and clinically applicable intervention by considering both physiological and perceptual responses, thereby supporting decision-making in clinical and sports settings.

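### The complete-case comparison does not reliably test the missing-at-random assumption, and its pooled 10% trigger is insensitive to missing 72 h MVIC in the key PBM versus IPC contrast

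*Protocol article*

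**What the plan says.** All references are to the Statistical analysis plan section of the protocol article unless stated otherwise.

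- **Primary handling.** All randomised participants are analysed as assigned. Missing MVIC is handled in the mixed model "using maximum likelihood estimation under a missing-at-random assumption".
- **Check.** The only sensitivity analysis named compares that result with complete cases: "a complete-case analysis will be performed if missing outcome data exceed 10% of the primary outcome observations". The threshold is not specific to a visit or an arm.
- **What is tested.** The primary inferential test is the group × time interaction over three groups and all time points. The section also fixes one contrast: "The prespecified key contrast will be the between-group difference in change in MVIC from baseline to 72 h between the PBM and IPC groups".
- **Size.** "45 participants (15 per group) were planned to ensure balanced allocation". The Abstract gives the schedule: "Outcomes will be assessed at baseline, immediately after exercise (only MVIC), and at 24-, 48-, and 72-hours post-exercise". MVIC is therefore measured five times.
- **Not stated.** The article gives no expected dropout rate and no expected reason for missing values. The step from 44 to 45 is attributed to balance, not to attrition.

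**The concern.** The exercise protocol is meant to damage the elbow flexors. The section on risks expects soreness, edema and fatigue, and participants are then asked for maximal contractions at 24, 48 and 72 h. A participant whose arm is sore and weak might skip a visit. The primary model contains group, time and a random intercept, but not soreness. Such loss is therefore missing at random only as far as the MVIC values already observed capture it. What remains is informative, and that is the part a sensitivity analysis should examine.

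Two features of the planned check look unsuited to this. Complete-case analysis discards data and leans on a stronger assumption instead of relaxing the one in doubt. And a threshold on all MVIC values dilutes loss at 72 h with values that are nearly certain to be present. At stake is whether the PBM versus IPC estimate at 72 h could be distorted by unequal loss without the plan showing it.

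**Working it through.** **Inputs.** 45 participants, 15 per arm, five MVIC measurements, correlation 0.79 (Statistical analysis plan); visit schedule (Abstract and Study design).

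**1. The plan's own sample size.** The inputs are a "three-group repeated-measures design with five measurements, α = 0.05, 80% power, f = 0.12", with "a within-participant correlation of 0.79, and ε = 0.82". Take λ = N·f²·m/(1 − ρ), df1 = (k − 1)(m − 1)ε and df2 = (N − k)(m − 1)ε, with ε applied to the degrees of freedom only.

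At N = 44:
- λ = 44 × 0.0144 × 5 / 0.21 = 15.09
- df1 = 2 × 4 × 0.82 = 6.56
- df2 = 41 × 4 × 0.82 = 134.48
- power = 0.810

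The minimum N is 44, as stated, and power at 45 is 0.821. This point uses only the resulting 45 participants.

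**2. Where the trigger falls.** 45 × 5 = 225 values, and 10% is 22.5. So 22 missing (9.8%) do not trigger and 23 (10.2%) do. If baseline is not counted as an outcome observation, 45 × 4 = 180 and 10% is 18. Then 18 missing do not exceed the limit and 19 (10.6%) do. Of the 225 values, 90 (baseline and immediately post-exercise) are taken at the treatment visit.

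| Pattern of loss that does not trigger | Of 225 | Of 180 |
|---|---|---|
| Participants missing 24, 48 and 72 h | 7 (21 values, 9.3%) | 6 (18 values, 10.0%) |
| Participants missing 48 and 72 h | 11 (22 values, 9.8%) | 9 (18 values, 10.0%) |
| All 15 values of one arm at 72 h | 6.7% | 8.3% |
| Extreme: only 72 h values missing, any arm | 22 of 45 (49%) | 18 of 45 (40%) |
| Extreme: only 72 h values missing, PBM and IPC only | 22 of 30 (73%) | 18 of 30 (60%) |

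If the seven participants in the first row were all in one arm, that arm would lose 7/15 = 47% of its 72 h values. In the third row the key contrast could not be estimated from a model with categorical time by group, yet the rule would still not trigger.

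**3. What the comparison shows when it does run.** This was simulated with 15 per arm (PBM, IPC), unit SD, equal correlation 0.79, a true difference of zero, 7 of 15 IPC values missing at 72 h, and 2,000 runs. The likelihood estimate used the known correlation. The missingness mechanisms are assumptions, not facts from the protocol. Bias in the PBM − IPC change to 72 h, in SD units:

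| IPC values lost at 72 h are those with the lowest | Maximum likelihood | Complete case |
|---|---|---|
| Change to 48 h (observed, so missing at random) | 0.00 | −0.22 |
| Part of the 72 h value not predicted by earlier values | −0.34 | −0.34 |
| Level at 72 h | −0.18 | −0.14 |
| Change to 72 h | −0.27 | −0.44 |

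In the first row the methods disagree although maximum likelihood is right. In the second they agree although both are wrong. In the third they differ little and both are biased. In the fourth they clearly differ, but both are biased. Neither agreement nor disagreement identifies the problem.

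**4. What a delta adjustment examines.** Lowering the imputed values by δ kgf in an arm with 7 of 15 missing moves that arm's 72 h mean, and hence the contrast, by 7/15 × δ = 0.47δ. The complete-case comparison does not examine this quantity.

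**The case against.** Several stronger readings are tempting, and the documents do not support them.

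- **That bias is likely.** The article gives no dropout rate or mechanism. Participants are healthy men aged 18–35, followed for 72 h. Each can contribute up to four earlier MVIC values with a pilot correlation of 0.79. Weakness that later causes a missed visit may already be visible in those values, and the likelihood analysis then handles it. Informative missingness is plausible, not shown.
- **That the check cannot detect bias, or would simply confirm a biased answer.** The last row of the simulation table contradicts this. What stands is that the comparison is unreliable in both directions.
- **That the trigger is wrong for the whole primary analysis.** The primary test uses every group and time point, so a denominator of all MVIC observations matches it. The mismatch is with the key contrast.
- **That half of all 72 h values could routinely go missing unnoticed.** Across all arms the limit is 49%, not half, since 23 of 45 would trigger. It also requires every missing value to fall at 72 h. With loss of all three follow-up visits the limit is 7 of 45 participants (16%).
- **That no other sensitivity analysis exists.** The article is condensed and a fuller analysis plan may add more. The complete-case choice and its trigger are nevertheless fixed here, so they can be judged as written.

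It is also fair to say that a full set of shifted analyses for one missing value would be out of proportion. The trigger proposed below allows for this.

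**Conclusion.** The point holds in a limited form. As a check on missing at random, the complete-case comparison is poorly chosen. It generally rests on a stricter assumption, and under the assumed mechanisms it gave both false reassurance (−0.34 against −0.34 SD) and a false alarm (0.00 against −0.22 SD). The trigger fits the overall interaction test but is insensitive for the PBM versus IPC contrast, which rests on 30 values at 72 h. The counts are exact given 45 participants and the chosen denominator of 225 or 180. The bias figures depend on the simulated mechanisms. The practical weight is modest if 72 h attendance is good and grows if it is poor or unequal between arms.

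**What to change.** Replace the complete-case comparison with a delta-adjusted (tipping-point) analysis of the PBM − IPC difference in MVIC change to 72 h. Multiply impute missing MVIC under missing at random, then lower the imputed values by increasing amounts over a stated kgf range, separately by group. Report the shift at which the conclusion changes.

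Base the trigger on missing 72 h MVIC in the PBM and IPC arms, either any missing value or a small number fixed in advance. For comparison, a 10% rule on those 30 values would act at 4 missing (13.3%), against 23 missing anywhere under the present rule. Report missingness and its reasons by arm and visit in every case.

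The cost is a little more programming and no new measurements. Recruitment had not begun at submission (Study design), so the change can be made before any data exist. If almost no 72 h values are missing, the analysis will add little information.

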## Discussion

This study protocol is designed to compare the effectiveness of PBM and IPC as preconditioning strategies to attenuate EIMD. It is hypothesized that PBM may provide greater attenuation of EIMD than IPC, as well as more favorable perceptual responses. Although previous studies have reported beneficial effects of both PBM and IPC on markers of EIMD [23, 30], findings remain heterogeneous and direct comparisons between these interventions are lacking. Therefore, the present trial is expected to help clarify their relative effectiveness and address an important gap in the literature through a controlled head-to-head comparison within the same experimental design. If both interventions are found to be equally effective, PBM may offer greater practical advantages in terms of feasibility. For example, in the present protocol, PBM will require 8.4 min of irradiation, whereas IPC will require 40 min and may generate discomfort due to the applied occlusion pressure.

In addition to physiological outcomes, this study will also examine perceptual responses, which may play a relevant role in the applicability of preconditioning strategies in real-world settings. Discomfort, affective valence, and perceived effort may influence adherence and acceptance of these interventions in both clinical and sports contexts. Therefore, the inclusion of these outcomes is expected to provide a more comprehensive understanding of the potential benefits and limitations of PBM and IPC beyond traditional markers of muscle damage.

This study protocol was developed following rigorous methodological standards, including allocation concealment, blinded participants, outcome assessment and statistical analysis, and intention-to-treat analysis. Furthermore, the use of individualized TRP is also expected to improve internal validity by standardizing the stimulus across participants.

This study has some limitations. First, the inclusion of only male participants may limit the generalizability of the findings to other populations, such as women and older adults. However, this approach was adopted to minimize potential hormonal influences on muscle strength and pain perception. Additionally, the restriction to a narrow height range, although potentially limiting external validity, was implemented to reduce variability in upper-limb lever arms and improve the consistency of MVIC measurements. Second, the study will assess only the relative percentage of TRP rather than the actual percentage of blood flow occlusion, which prevents precise quantification of the degree of vascular restriction. Another limitation is the absence of circulating biomarkers, such as creatine kinase. Nevertheless, EIMD will be evaluated using several well-established indirect markers, including MVIC, DOMS, ultrasound echo intensity, and range of motion. Finally, sensory differences between IPC and sham IPC may allow some participants to infer their group allocation. However, sham procedures were designed to mimic the active interventions, and blinding effectiveness will be assessed at the end of the study.

Overall, this study is expected to provide relevant evidence regarding the comparative effectiveness and practical applicability of PBM and IPC as preconditioning strategies. The findings may contribute to improving decision-making in both clinical and sports settings, particularly in the selection of feasible and well-tolerated interventions to mitigate EIMD.

